## Abstract

**Background:**

A substantial body of research has established the effectiveness of brief interventions for problem *alcohol use.* Following these studies, national dissemination projects of screening, brief intervention (BI), and referral to treatment (SBIRT) for alcohol *and drugs* have been implemented on a widespread scale in multiple states despite little existing evidence for the impact of BI on drug use for non-treatment seekers. This article describes the design of a study testing the impact of SBIRT on individuals with drug problems, its contributions to the existing literature, and its potential to inform drug policy.

**Methods/design:**

The study is a randomized controlled trial of an SBIRT intervention carried out in a primary care setting within a safety net system of care. Approximately 1,000 individuals presenting for scheduled medical care at one of seven designated primary care clinics who endorse problematic drug use when screened are randomized in a 1:1 ratio to BI versus enhanced care as usual (ECAU). Individuals in both groups are reassessed at 3, 6, 9, and 12 months after baseline. Self-reported drug use and other psychosocial measures collected at each data point are supplemented by urine analysis and public health-related data from administrative databases.

**Discussion:**

This study will contribute to the existing literature by providing evidence for the impact of BI on problem drug use based on a broad range of measures including self-reported drug use, urine analysis, admission to drug abuse treatment, and changes in utilization and costs of health care services, arrests, and death with the intent of informing policy and program planning for problem drug use at the local, state, and national levels.

**Trial registration:**

ClinicalTrials.gov NCT00877331

## Background

A substantial body of research has established the efficacy and effectiveness of brief (one to two sessions) interventions (BI) for excessive or hazardous alcohol use in patients seen in medical settings, both primary care and emergency department (ED) [1-3]. Following these studies, national dissemination projects of screening, brief intervention, and referral to treatment (SBIRT) for alcohol *and drugs* have been implemented on a widespread scale in multiple states [4,5]. Some have argued that this rapid progression of BI from efficacy to effectiveness to dissemination for drugs other than alcohol has outstripped its evidence base [6]. For example, there have been few randomized controlled trials of BI for drug abuse in the general medical setting for non-treatment seekers [7,8], leading the US Preventative Services Task Force to conclude that the utility of BI in medical settings as an opportunistic intervention for drug abuse remains unclear [9]. Thus, from a policy perspective, an important but still unanswered question is whether BI reduces drug use.

According to a recent epidemiological study, a disproportionate number of individuals with drug abuse or dependence are from lower socioeconomic strata [10], where access to specialized substance abuse treatment is difficult and, as a result, exacerbates the motivational challenges and follow-through that BI targets. Such individuals, who are often uninsured or on Medicaid, face daunting and diverse barriers to health care access and are usually served in public sector safety net medical settings (hospitals and community health clinics). Few of these individuals seek specialist chemical dependency treatment [11]. The related costs of untreated drug abuse are substantial [12-14]. Updated data on such costs and public health-related adverse effects are needed by policymakers to create the necessary traction to drive policy changes to improve provision of drug treatment. In this regard, ambulatory primary care is an important setting to test the effectiveness of BI on drug abuse since, were it effective, modest effects for a large number of patients would yield a sizable public health benefit [15].

Accordingly, this study was designed to evaluate the impact of a BI on patients with problem drug use in a primary care setting within a safety net system of care. It is intended to serve as a policy-relevant randomized controlled trial with broad external validity. It builds upon the significant knowledge base acquired in the study of brief interventions in medical settings for alcohol abuse including a well-documented intervention utilizing motivational interviewing (MI) [16-18] and a growing literature that focuses on public health outcomes of BI [19,20]. It is unusual in its focus on providing BIs to individuals with evidence of *drug dependence and abuse* in primary care. As such, its design and implementation has required consideration of a number of factors that, prior to this point in time, have not been relevant to the study of BIs. The purpose of this paper is to describe the design as well as the rationale for key decisions made in this study with the intent of informing future studies with a focus on BI in drug abuse.

## Methods and design

### Specific aims

The primary focus of the study is to evaluate the impact of a BI on patients with problem drug use and abuse seen in a primary care clinic at a large safety net hospital by comparing outcomes among patients randomly assigned to one of two conditions: (i) BI, consisting of one encounter during a routine primary care medical visit with a brief follow-up phone booster and referral to treatment when indicated; and (ii) enhanced care as usual (ECAU) consisting of problem notification and referral during a routine primary care medical visit. Specific aims are to: (1) Examine whether BI is effective compared to ECAU at reducing drug use and improving psychiatric and select psychosocial outcomes in individuals with a spectrum of problem drug use; (2) Test whether interventionist fidelity to the BI model is associated with better outcomes; (3) Estimate the impact of the BI on several public health outcomes that are directly related to the hazardous effects of illicit drug use including the use of acute health care services, involvement in the criminal justice system, HIV risk behavior, and mortality; and (4) Estimate the costs of the intervention, potential cost offsets, and its incremental cost-effectiveness from the payer perspective based on health care service use and drug use frequency.

### Study design

This study is a two-group randomized prospective trial with blinded assessments (See Figure 1), approved by the University of Washington Institutional Review Board (Protocol #34892). Written informed consent is obtained from patients for study participation including permission to use unidentified information collected from them in study reports. Approximately 1,000 individuals presenting for scheduled medical care at one of seven designated primary care clinics who endorse problematic drug use when screened during that visit and then randomized in a 1:1 ratio to BI versus ECAU using a stratified permuted block randomization procedure. The purpose of the stratification is to balance random assignment by three factors known to be related to substance abuse outcomes including severity of drug problem [21], presence of a co-occurring mental disorder [22], and readiness to change [23].

**Figure 1 F1:**
[figure not shown]
Study design.

Individuals randomized to the BI group receive screening, a single-encounter BI with referral to treatment when indicated, and a single follow-up phone contact approximately one week later. Individuals assigned to ECAU receive screening, a handout with the results of their drug screen, the risk associated with their drug use, and a list of referrals to chemical dependency treatment. Individuals in both groups are re-assessed at 3, 6, 9, and 12 months after baseline. All assessments are carried out in person wherever possible, with phone interview as a back-up option. Persons conducting follow-up assessments are blinded to the participant’s intervention versus control group assignment.

### Two-arm design: BI versus usual care

A two-arm design was adopted in order to assess the effects of the BI over and above usual care. However, the clinic sites where recruitment takes place for this study offer patients more options than may be available in other safety net medical settings across the country. This fact coupled with the ethical need to provide referral following screening of dependent patients led to defining the control condition as ECAU. This condition provides a test of whether BI is better than a less expensive but relatively high quality usual-care option, as opposed to being better than no intervention at all (neither systematic screening nor follow-up of screen-positive patients) and, as such, represents a rigorous comparison.

### Influence of the SAMHSA SBIRT dissemination program

Washington State received an SBIRT grant from the Substance Abuse and Mental Health Services Administration (SAMHSA) in 2003 that placed chemical dependency professionals trained in BI and associated MI skills into the emergency departments (EDs) of nine hospitals across the state (“WASBIRT”) [20]. The site of the current study is one of these hospitals. In order to build upon the strengths of these WASBIRT ED services and to maintain consistency with them, the current study is set up to mirror the WASBIRT design to the extent that is both reasonable and possible. This includes using the Drug Abuse Screening Test (DAST-10) to estimate drug use severity, using physician extenders to deliver the intervention, and using a single 30–45 minute BI session.

When SAMHSA funding ended in 2008, local resources were made available to sustain SBIRT services in the ED at the site of the current study. This created two potential confounds. One, enrolled patients may receive a previous BI, and two, they may receive a subsequent BI. To control for these potential confounds, we use administrative data. Subsequent exposure is used as an outcome because those receiving a BI in the current study might be more open to receive an additional one, suggesting a useful metric for assessing intervention value.

### Defining the population

As stated earlier, the population of interest is individuals seeking primary care treatment in a safety net medical center setting. Screening procedures are designed to identify individuals with problem drug use along a continuum of severity. Study inclusion criteria include adults age 18 and over; having used an illegal drug or used a prescription medication for nonmedical reasons at least once in the past three months [24] (equivalent to a DAST-10 score greater than 0 [25,26]); currently receiving care in the primary care clinic and planning to continue such care for the next year; English speaking and able to read and understand screening and assessment forms (6^th^ grade literacy); and having a phone, easy access to a phone with voicemail, or access to e-mail in order to facilitate scheduling.

To enhance external validity there are few baseline exclusion criteria. They include having attended formal treatment for substance abuse (excluding self-help groups such as Alcoholics Anonymous) in the past month; life-threatening medical illness (potential mortality in next year); severe cognitive impairment or active psychosis interfering with cognitive ability to process the BI (based on performance during consent and assessment); or active high risk suicidality [27].

There are two reasons for not excluding patients with the most severe drug problems from this trial. First, although some studies of BI for alcohol have found that patients with alcohol dependence responded less well to a BI than patients with less severe abuse or hazardous drinking, Field recently found that patients with alcohol dependence responded better to a BI than those with less severe problems [28] and Cobain found hospital-based BI effects to be independent of baseline dependence or medical comorbidity [29]. Second, even if a BI were inadequate as a stand-alone treatment for safety net patients with severe drug dependence, BI may prove to be a valuable referral mechanism for getting these patients to more intensive chemical dependency treatment, as it did in WASBIRT [30]. For these reasons, we include individuals across the full range of drug use and abuse in the present study. To balance drug use severity across BI and control groups, we use the DAST-10 score as a stratifying variable.

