All brief interventions are audio-recorded and are scored by trained coders using the Motivational Interviewing Treatment Integrity (MITI) instrument [47] to monitor potential drift in the MI protocol as well as to assess for Aim 2 levels of fidelity to MI. While all interventionists are required after training to reach and maintain a specified threshold of MI skill, it is expected there will still be adequate variation in MI skills to allow for an analysis of study Aim 2—testing the degree to which fidelity to the BI model is associated with better outcomes.

It is possible that the intervention may be too brief to have a treatment effect for some patients with severe drug disorders. However, the intervention could still contribute to a referral effect in that patients who participated in a BI may be more likely to seek treatment after being referred. Whether to refer a patient to treatment is determined using the DAST-10 score as a guide in concert with the spirit of the patient-interventionist interaction. After the intervention, a referral to treatment is usually offered if the patient is not overtly hostile to the idea and when the DAST-10 score is 6 or greater in accordance with existing norms [21]. A DAST-10 score less than 3 does not generally trigger a referral. For DAST-10 scores between 3 and 5, the interventionist uses their judgment as to whether to refer based on information obtained from the BI. When in doubt, or whenever the patient asks for help, the interventionists refer. In addition, to preserve internal validity, all individuals assigned to the BI group are given the same referral sheet as individuals assigned to the ECAU group.

A booster session has been shown to enhance the effects of a BI [48] and, for this reason, is included in the present study. The booster session consists of a ten-minute follow-up call approximately one week after the initial intervention. During the call, the interventionist references the plan or option decided upon in the initial intervention and uses MI to follow-up on ambivalence about enacting the plan, generating change talk, or committing to specific goals.

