**Data source**	**Owners of data**	**Description of data records**	**Derived measures**
Treatment and Assessment Report Generation Tool (TARGET)	Washington State Department of Social and Health Services (DSHS), Division of Behavioral Health and Recovery (DBHR)	Record of participation in publicly-funded chemical dependency treatment or detoxification services	- Number of days with outpatient treatment visit
			- Number of days of inpatient stays
			- Number of detoxification admissions
Medical records	Medical Center Site of Study	Health care encounters by date, diagnoses	- Number of inpatient hospital stays/days
			- Number of emergency department visits
			- Number of outpatient visits
			- HIV diagnosis date
			- Hepatitis diagnosis date
Billing records	Medical Center Site of Study	Cost of health care encounters by date	Cost of
			-Inpatient hospital stays
			- Emergency department visits
			- Outpatient visits-
Comprehensive Hospital Abstract Reporting System (CHARS)	Washington State Department of Health (DOH)	Hospital discharge data, length of stay, up to 17 diagnoses, demographic information	- Number of inpatient hospital stays/days
Washington State Patrol Arrest Records	Washington State Patrol	All arrests in Washington State including arrest date, nature of offense, level of offense	- Number and type of felony arrests
			- Number and type of gross misdemeanor arrests
Washington State Death Records	Washington State DOH Vital Records	Information about decedent (e.g., age, date of birth, race), place of death, cause-of-death codes, injury information	- Date of death
			- Cause of death

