### Choosing the primary outcome variables

Outcome variables were selected specific to each of the study’s aims:

#### Aim 1

For the first aim—to examine whether BI is effective at improving drug use, psychiatric outcomes, select psychosocial outcomes, and attendance in drug abuse treatment—it is important to reliably capture changes in drug use as well as in other variables in as brief a period of time as possible. Because of its widespread use, brevity, and reliability, the validated short form of the Addiction Severity Index (ASI), the ASI-Lite [55], was selected for this purpose along with the Treatment Services Review (TSR) [56]. To further minimize time burden on participants, we only administer items required to compute the ASI composite scores (half the total items) [55].

In order to identify changes in illicit drug use, we use items from the ASI drug section to measure days of any drug use. A urine toxicology screen is used to supplement participants’ responses. In addition, we use the ASI composite scores as comprehensive measures of participants’ medical, psychiatric, legal, family/social, and employment status. The HIV Risk-Taking Behavior Scale is used to assess risk-taking behavior among intravenous drug users [57] and the EQ-5D-3L is used to measure health status [58]. Administrative data are used to supplement ASI data on legal (e.g., arrests) effects. Changes in attendance in drug treatment are obtained from the TSR as well as from state administrative chemical dependency treatment records.

#### Aim 2

The second aim—to test whether fidelity to the BI model is associated with better outcomes—requires a reliable way to assess fidelity. Because of is reliability, cost effectiveness, and brevity, the MITI, which provides a standardized way to rate session audiotapes for degree of MI content, was selected for this purpose [47]. Outcomes for this aim include changes in illicit drug use and drug treatment attendance as measured in the first aim.

#### Aim 3

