For the third aim—to estimate the impact of BI on select public health outcomes that are directly related to the hazardous effects of illicit drug use—it is important to identify objective measures reflective of the consequences of illicit drug use. Because of their established tie to illicit drug use, we selected changes in utilization of health care services (including ED visits, inpatient hospitalizations, and hospital days), arrests, and death, as captured in state administrative records [59,60].

#### Aim 4

The fourth aim—to estimate the cost of the intervention, potential cost offsets, and its incremental cost effectiveness —requires valid cost data. The cost of the intervention includes the cost of personnel, materials, and locations for start-up and implementation activities required to screen for drug use and provide a BI. Potential cost offsets will be examined for emergency room visits, outpatient visits, and hospital admissions. The cost measure for all of these medical services includes the direct and indirect costs of providing medical care from the provider perspective. If indicated by study results, we will also assess cost offsets generated by reductions in arrests. If the BI is found to reduce drug use, we will further estimate the incremental cost of the BI intervention compared to its incremental effect on drug use.

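### Aim 3 is framed as acute care use but measured by all hospital stays and days, so hospital-based addiction treatment prompted by BI could offset a real fall in acute admissions

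*Protocol article*

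**What the plan says.** Four parts of the protocol article bear on this.

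- **Expected mechanism.** Defining the population gives, as one reason for not excluding severe users, that "BI may prove to be a valuable referral mechanism for getting these patients to more intensive chemical dependency treatment". Specific nature of the intervention repeats the idea: even where BI is too brief to treat, "the intervention could still contribute to a referral effect in that patients who participated in a BI may be more likely to seek treatment".
- **Aim 1.** Under Choosing the primary outcome variables, the aim is "to examine whether BI is effective at improving drug use, psychiatric outcomes, select psychosocial outcomes, and attendance in drug abuse treatment". On sources: "Changes in attendance in drug treatment are obtained from the TSR as well as from state administrative chemical dependency treatment records". Table 2 describes the state treatment file as a "Record of participation in publicly-funded chemical dependency treatment or detoxification services". Its derived measures are outpatient treatment days, inpatient days and, as a separate line, "Number of detoxification admissions".
- **Aim 3, the construct.** Specific aims names acute care use tied to the hazards of illicit drug use.
- **Aim 3, the measure.** Choosing the primary outcome variables selects health care utilization ("including ED visits, inpatient hospitalizations, and hospital days"), arrests and death, on the ground that they reflect what drug use leads to. For both the site's medical records and the state discharge file, Table 2 derives "Number of inpatient hospital stays/days". Neither place limits the count by reason for admission.

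The section on choosing primary care over the ED states the expected direction: lower risk should prevent costly ED and hospital visits.

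**The concern.** The construct and the measure differ. A planned stay for detoxification or addiction treatment that follows a BI referral is not acute use in the sense of the Specific aims. Nor is it simply a consequence of drug use; in part it is a consequence of the intervention. If it takes place in a hospital that either file covers, it still enters the Aim 3 count.

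Such stays would not be balanced between arms, because the trial hopes that BI raises treatment entry. Randomization does not remove the difference, since it arises after assignment and through the intervention. The better BI works as a route into treatment, the more the all-stay count could hide a true fall in acute drug-related admissions. Aim 3 is meant to inform policy, so a null or adverse inpatient result produced in this way could be misread.

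**Working it through.** The article states no hospitalization rate, referral uptake or Aim 3 power, so there is no figure to reproduce. What can be worked out is how large the excess must be to matter.

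**Input from the article:** 500 patients per arm (Power analysis).

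**Assumptions, not in the article:**
- *r*: acute stays per ECAU patient over follow-up: 0.2, 0.4 or 0.8.
- *q*: true relative reduction in acute stays under BI: 5%, 10% or 20%.
- *t*: hospital-based treatment stays per ECAU patient.
- *e*: between-arm excess of such stays per BI patient.

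**Formula.** All-stay rate ratio = [r(1 − q) + t + e] / (r + t). It exceeds 1 when e > q × r. The threshold does not depend on *t*, so treatment stays that occur equally in both arms do not move it.

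**Break-even in stays among 500 BI patients (500 × q × r):**

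| r | q = 5% | q = 10% | q = 20% |
|---|---|---|---|
| 0.2 | 5 | 10 | 20 |
| 0.4 | 10 | 20 | 40 |
| 0.8 | 20 | 40 | 80 |

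That is 1 to 16 excess stays per 100 BI patients.

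**Rate ratio at r = 0.4, q = 10%, t = 0.** The acute-only ratio is 0.90 throughout. The all-stay ratio is:
- e = 0: 0.36/0.4 = 0.90
- e = 0.02: 0.38/0.4 = 0.95
- e = 0.04: 0.40/0.4 = 1.00
- e = 0.06: 0.42/0.4 = 1.05
- e = 0.10: 0.46/0.4 = 1.15

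**Break-even in hospital days.** Assume 2 acute days per ECAU patient and q = 10%. The true saving is 500 × 2 × 0.10 = 100 days. It is cancelled by 100/3 ≈ 33 excess stays of 3 days, 100/5 = 20 of 5 days, or 100/21 ≈ 5 of 21 days. Days are therefore more exposed than stays if covered treatment stays are long.

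**Who can contribute.** Per Specific nature of the intervention, referral is usually offered at a DAST-10 score of 6 or more and generally not below 3, so the excess must come from part of the arm. If half the arm were referred (assumed), 20 stays would be 20/250 = 8 per 100 referred patients.

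**The case against.** The strongest objection is that the overlap is not shown. Table 2 lists addiction treatment and hospital care as separate records with separate owners. The article nowhere says that detoxification or treatment stays occur in hospitals covered by the discharge file or the site's records. Stays in free-standing facilities would appear only in the treatment file and would cause no conflict. This stands, and it is why the size may be zero.

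A second objection is that the Specific aims already say acute, and that coding rules belong in a fuller plan. The first half is true but cuts the other way: the places that specify the measure do not carry the restriction over. The second half stands in part. A fuller document may contain such a rule, so the point is the mismatch between construct and stated measure, not missing coding detail.

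Third, all-stay use by randomized arm is a legitimate intent-to-treat quantity, and dropping stays by a post-randomization feature could remove true acute drug-related admissions. This stands, and it rules out replacing the all-stay count.

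A reader might go further and infer that the same detoxification stay is scored as a gain in Aim 1 and a harm in Aim 3, so that the aims contradict each other. The article does not support this. Aim 1 speaks of treatment attendance and does not say that detoxification counts as attendance; Table 2 lists detoxification admissions on their own line. Harm is not the article's term. BI can raise both treatment use and total hospital use without contradiction. Nor would such stays arise in the BI arm alone: Study design gives ECAU patients a referral list, and BI patients receive the same sheet, so only the between-arm excess matters.

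**Conclusion.** The point holds in conditional form. Aim 3 is about acute use, and the inpatient measure as specified is not limited to it. To the extent that detoxification or addiction-treatment stays occur in covered hospitals, an excess in the BI arm would offset a true fall in acute drug-related hospitalization. Under the assumed rates a modest excess is enough to cancel the effect, but the article supplies none of those rates. Reversal of the inpatient result is possible, not demonstrated.

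The matter is confined to the inpatient part of Aim 3 and to how the hospital-admission cost offsets in Aim 4 are explained. It does not touch the drug-use outcome. It is worth correcting because the correction is cheap.

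**What to change.** Keep the all-stay intent-to-treat count. Beside it, by a rule fixed before any comparison of arms, report:

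- (a) acute stays and days;
- (b) planned addiction-treatment or detoxification stays, flagged by principal diagnosis or service and by date match to the state treatment file.

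Base the Aim 3 statement about acute use on (a), with the all-stay count as a check. Show detoxification admissions separately and do not read them as treatment attendance, since they can mark relapse as well as engagement. Keep all stays in the Aim 4 costs.

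The cost is a linkage and coding rule on files already planned. Table 2 gives the discharge file length of stay and up to 17 diagnoses, and the site's records encounter dates and diagnoses. It does not list dates for the treatment file, but its day counts imply them; this should be confirmed. Some stays will be misclassified, and the treatment file covers only publicly funded care, so matching will be incomplete. Showing the all-stay count alongside makes both limits visible.
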